**Methods/Design:**

This trial uses a multicentre, parallel-group, randomized, sham acupuncture and shallow acupuncture, controlled single-blind design. Nine hospitals are involved as trial centres. 945 patients who meet inclusion criteria are randomly assigned to receive optimized acupuncture therapy, sham acupuncture or shallow acupuncture by a computerized central randomization system. The interventions past for 4 weeks with eight to ten treatments in total. The group allocations and interventions are concealed to patients and statisticians. The Northwick Park Neck Pain Questionnaire (NPQ) is used as the primary outcome measure, and the McGill Pain Questionnaire (MPQ) and The Short Form (36) Health Survey (SF-36) are applied as secondary outcome measures. The evaluation is performed at baseline, at the end of the intervention, and at the end of the first month and the third month during follow-up. The statistical analyses will include baseline data comparison and repeated measures of analysis of variance (ANOVA) for primary and secondary outcomes of group and time differences. Adverse events (AEs) will be reported if they occur.

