### Sample size calculation

The size calculation is based on the mean and standard deviation (SD) for NPQ from a pilot study [1]. The reported pilot study was a two-arm design with a treatment group and one placebo group, whereas this trial protocol is a three-arm design with one treatment group (OAT) and two control groups (sham group and shallow group). The mean ± SD of the treatment group reported in the pilot study (20.71 ± S 11.91) [1] were used as the expected values of the OAT group, and the mean ± SD of the placebo group (24.04 ± 11.83) were used as the expected values of the two control groups. The software Power Analysis and Sample Size (PASS; version 11; NCSS Statistical Software, Kaysville, UT, USA) was used to perform the sample size calculation.

The sample size was calculated with a significance level of 0.05 and power of 0.90. The result was a total required sample size of 732, with 244 for each group. With a maximum dropout tolerance of 15%, 32 patients per center are needed for each group, or 94 patietns overall per center. Therefore, 846 patients are needed for the trial, with 288 for each group across the nine centers.

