### Statistical analyses

EpiData software (version 3.1 is used for data entry, and SPSS (version 16.0; SPSS Inc., Chicago, IL, USA) for statistical analyses. The analytic strategy includes the descriptive analysis of the demographic characteristics and the baseline data for the primary and secondary outcomes. The group differences are tested by analysis of variance (ANOVA) for continuous variables, the Kruskal-Wallis test for ranking variables, and the χ² test for categorical variables. The significance level is set at α = 0.05, two-sided.

There are four measuring points set to assess the efficacy of the OAT, as described above in the Outcomes section. Therefore, we will apply the two-factor repeated measures analysis of variance (ANOVA) model with the time of measure as the within-subjects factor and treatment as the between-subjects factor (significance level α = 0.05, two-sided). In addition, stratification analysis will be used to explore the potential effect difference between centres.

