Considering the trial results, both pain intensity and physical function are subjective feelings, therefore, we will use the PRO and the validated scales and questionnaires to assess the clinical outcome. For the evaluation of CS neck pain, three aspects were included in the complete assessment: neck pain, physical function, and QOL. The NPQ will be used as the primary outcome to evaluate CS-related neck pain, radiculopathy. and impairment of daily functions, while for the secondary outcomes, the MPQ will measure the pain intensity in general settings, and the SF-36 will measure patient QOL changes caused by changes in physical and mental conditions.

Salter *et al *. [12] proposed a protocol for an RCT to evaluate the effect of acupuncture for neck pain, recommending 229 cases for each arm based on the assumption of 90% power to detect a five-point NPQ difference, a 5% significance level, and a 14% drop-out rate during follow-up. In our study, a total of 945 cases are required from 9 centres, therefore, there will be 315 cases for each arm, and at least 268 cases are required to complete the trial and follow-up. The report of the study results will follow the CONSORT 2010 guidelines [13], and the operation details for acupuncture will be reported in accordance with the 2010 CONSORT-STRICTA extension [14] guidelines. Thus, this study will be able to provide high-quality evidence for the efficacy of the OAT for CS neck pain.

In conclusion, the multi-centre RCT design of this trial will be able to assess and differentiate the effects of the OAT.

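### The recruitment target is stated inconsistently: Methods prints 846 beside figures that imply 864, the abstract and Discussion require 945, and nothing reconciles them

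*Protocol article*

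**What the plan says.** Sample size calculation takes its expected NPQ values from a pilot study: 20.71 (SD 11.91) for OAT and 24.04 (SD 11.83) for each of the two control groups. It states: "The sample size was calculated with a significance level of 0.05 and power of 0.90". The result is given as 732 in total, 244 per group. Allowing for at most 15% dropout, it continues that "32 patients per center are needed for each group, or 94 patietns overall per center", and ends: "Therefore, 846 patients are needed for the trial, with 288 for each group across the nine centers".

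Other sections give a different size. The abstract says "945 patients who meet inclusion criteria are randomly assigned". The Discussion says "a total of 945 cases are required from 9 centres, therefore, there will be 315 cases for each arm", and adds that "at least 268 cases are required to complete the trial and follow-up".

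The sample size section does not name the test behind 244, and the Discussion does not name one behind 268. Statistical analyses plans ANOVA across groups and a repeated measures ANOVA; on the error rate it says "The significance level is set at α = 0.05, two-sided". Interventions hypothesises that OAT is superior to both the placebo and the non-specific effects.

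**The concern.** Two faults overlap. Within Methods, the per-group and overall figures cannot both be right. Between sections, Methods gives one recruitment target and the abstract and Discussion give another, each presented as what the trial needs.

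Trial status says that patients are being recruited. The Methods figure implies stopping at 94 patients per centre and the abstract figure at 945/9 = 105. With two published targets, a reader of the results could not tell which size was planned, and stopping at either could be questioned later. The article also does not say which comparison the 90% power refers to, and the answer depends on that.

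**Working it through.** **Inputs.** Means 20.71, 24.04 and 24.04; SDs 11.91 and 11.83; α = 0.05; power 0.90; maximum dropout 15%; nine centres; three equal groups (all from Sample size calculation). Two-sided testing is taken from Statistical analyses. Difference: 24.04 − 20.71 = 3.33. Pooled SD: √[(11.91² + 11.83²)/2] = 11.87.

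**1. Reproducing 244.** For a one-way ANOVA F test with three groups, the overall mean is (20.71 + 24.04 + 24.04)/3 = 22.93. The sum of squared deviations is 2.22² + 1.11² + 1.11² = 7.393. The noncentrality is λ = n × 7.393/SD², on 2 and 3n − 3 degrees of freedom.
- SD 11.91, n = 244: λ = 12.72, power 90.0%. This is the smallest n that reaches 90%, so 244 per group and 732 in total are reproduced.
- SD 11.87: the smallest n is 243.

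**2. Carrying 244 forward.**
- 244/0.85 = 287.06, rounded up to 288 per group
- 288/9 = 32 per centre per group, as printed
- 3 × 32 = 96 per centre (printed: 94)
- 9 × 96 = 3 × 288 = 864 in total (printed: 846)
- 846 = 9 × 94, so the total follows from the wrong per-centre figure
- 846/3 = 282 per arm, and 282 × 0.85 = 239.7, below 244

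**3. The 945 set.** 945/3 = 315 per arm; 315/9 = 35 per centre per arm; 315 × 0.85 = 267.75, about 268. These figures agree with one another.

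**4. A test that gives 268.** For a two-sided two-sample t test of OAT against one control, the normal approximation is n = 2 × 11.87² × (1.960 + 1.282)²/3.33² ≈ 267. The exact noncentral t calculation gives 268 per arm (power 90.0%).

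**5. Power at each total after 15% dropout** (SD 11.87, two-sided 0.05, no multiplicity adjustment). The t test noncentrality is 3.33/(11.87 × √(2/n)).

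| Total | Status in the article | Per arm | Completers per arm | Three-group F test | OAT vs one control |
|---|---|---|---|---|---|
| 846 | printed | 282 | 239.7 | 89.7% | 86.5% |
| 864 | implied by 288 per group | 288 | 244.8 | 90.3% | 87.2% |
| 945 | printed | 315 | 267.75 | 92.8% | 90.0% |

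With SD 11.91, the F test figure at 846 is 89.5%.

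**6. Differences in size.** 945 − 846 = 99 patients (11 per centre). 945 − 864 = 81 (9 per centre). 864 − 846 = 18 (2 per centre).

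**The case against.** The strongest reply is that little power is at stake. Methods does not claim 90% power for a pairwise comparison, and the planned analysis is an ANOVA across groups. For the three-group test that reproduces 244, power is about 90% or better at every total. A reader might infer that the trial is underpowered or that its 90% is lost. The documents do not support that: power falls below 90% by more than a fraction of a point only if the relevant test is OAT against a single control. The shortfall at 846 is also small, about 4 completers per arm. It arises only near the stated maximum dropout, since 282 per arm still leaves 244 at dropout of up to 1 − 244/282 = 13.5%. All of this stands.

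A reader might also infer that the two sets were deliberately derived from two different tests. The article does not say so. The match to 244 needs SD 11.91 and not the pooled 11.87, and 268 could simply be 315 less 15%, rounded up. The link is therefore an inference, and the sponsor should not be asked to adopt it as the derivation.

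Nor do the documents show which number the centres are working to, so a premature stop at 846 is a possibility and not an established fact. And 864 is implied by 288 per group; it is not printed as a target.

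The pairwise reading still has some basis, because Interventions hypothesises superiority to both controls. For that hypothesis even 945 needs careful wording. The power to win both unadjusted pairwise tests at 268 per arm is about 83% (normal approximation, correlation 0.5 between comparisons that share the OAT arm).

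None of this removes the contradiction. All the figures stand in current, intact sentences, and condensing a full protocol into an article would explain an omission but not two different targets.

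**Conclusion.** The point holds as an inconsistency that is wrong as written. Within Methods, 94 and 846 contradict 32 and 288, and 846 just misses the section's own 244 completers at maximum dropout. Between sections, 846 and 945 differ by 99 patients, and 244 and 268 completers differ by 24 per arm, with no reconciliation.

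The effect on power is modest and depends on the comparison. The three-group test has about 90% at 846 or 864 and about 93% at 945. OAT against one control has about 87% at 846 or 864 and about 90% at 945. These figures rest on the pilot means and SDs, two-sided α of 0.05 without multiplicity adjustment, equal arms and 15% dropout. The contradiction itself is plain arithmetic and needs none of these assumptions.

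**What to change.** State one recruitment target in the abstract, Methods and Discussion, and name the comparison it is sized for.

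- **If 945 is the operating target**, as the abstract and Discussion say, put 945 in total, 315 per arm, 35 per centre per arm and about 268 completers per arm into Methods. Give the sponsor's actual derivation, not one inferred from the numbers. Note that this size gives about 90% power for OAT against one control.
- **If the 244-completer calculation is kept**, correct 94 to 96 and 846 to 864, and change 945, 315 and 268 elsewhere to match (864, 288 and 244). State that 90% power applies to the three-group test, and that each comparison of OAT with one control has about 87%.

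The cost is a text correction and one notice to the nine centres. If they already work to 945, no patients are added. If they have been working to 94 each, adopting 945 adds 11 per centre (99 in all) and adopting 864 adds 2 per centre (18 in all). The sponsor should confirm which number is in use.

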### Statistical analyses

EpiData software (version 3.1 is used for data entry, and SPSS (version 16.0; SPSS Inc., Chicago, IL, USA) for statistical analyses. The analytic strategy includes the descriptive analysis of the demographic characteristics and the baseline data for the primary and secondary outcomes. The group differences are tested by analysis of variance (ANOVA) for continuous variables, the Kruskal-Wallis test for ranking variables, and the χ² test for categorical variables. The significance level is set at α = 0.05, two-sided.

There are four measuring points set to assess the efficacy of the OAT, as described above in the Outcomes section. Therefore, we will apply the two-factor repeated measures analysis of variance (ANOVA) model with the time of measure as the within-subjects factor and treatment as the between-subjects factor (significance level α = 0.05, two-sided). In addition, stratification analysis will be used to explore the potential effect difference between centres.

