#### Outcome measuring procedure and data collection

The outcomes will be assessed before the first treatment (baseline measurement), immediately after the final treatment (short-term outcome of therapeutic effect), and at the end of the first and third months after the final treatment (long-term effective outcomes). The data will be by PRO, with the questionnaires being completed by the participants themselves with necessary instruction from the researchers. Medication use at baseline, during the intervention, and at the 3-month follow-up will be recorded.

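### As written, the repeated measures ANOVA drops every patient who misses a visit (about 142 of 945 at the tolerated 15% dropout), which discards observed NPQ data and leaves the efficacy comparison open to attrition bias

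*Protocol article*

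**What the plan says.** The Statistical analyses section gives the efficacy method: "we will apply the two-factor repeated measures analysis of variance (ANOVA) model", with time as the within-subjects factor and treatment as the between-subjects factor at a two-sided 5% level. The same paragraph counts the levels of the time factor: "There are four measuring points set to assess the efficacy of the OAT". These are baseline, the end of treatment, and two follow-up visits, "at the end of the first and third months after the final treatment (long-term effective outcomes". The software is given as "SPSS (version 16.0; SPSS Inc., Chicago, IL, USA) for statistical analyses"; no particular SPSS procedure is named.

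The Sample size calculation section inflates the group sizes "With a maximum dropout tolerance of 15" per cent. The Discussion, working from 945 patients and 315 per arm, adds that "at least 268 cases are required to complete the trial and follow-up".

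**The concern.** A two-factor repeated measures ANOVA with time as a within-subjects factor treats each patient's four values as one complete record. The standard SPSS repeated measures procedure deletes a patient's whole record if any value is missing. Someone with NPQ at baseline, end of treatment and 1 month who misses only the 3-month visit then counts at no time point, including those where the outcome was observed.

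Two things are at stake. Observed outcome data are thrown away. And the comparison is no longer between the groups as randomised, but between those in each group who attended every visit. If attendance depends on outcome, and does so differently by arm, the contrast is biased. Enlarging the sample for dropout does not cure this, because it protects power only.

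The design leaves room for such dependence in either direction. Follow-up means returning to the clinic 1 and 3 months after treatment ends, and the treating doctors know the allocation. Both control arms receive needling to about 3 mm without de qi, so lack of relief might drive loss there. OAT is needled to 20 mm with manipulation, and the Safety evaluation section allows an adverse event to lead to withdrawal, so loss might also be driven in the OAT arm.

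**Working it through.** **Inputs.** NPQ 20.71 (SD 11.91) for OAT and 24.04 (SD 11.83) for each control; alpha 0.05, power 0.90, 244 per group, 15% dropout (Sample size calculation). 945 randomised, 315 per arm, 268 to complete (Discussion; the Abstract also gives 945). Four measuring points (Statistical analyses).

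**1. Reproduce the plan's figures.**
- Three-group F test: the grand mean is (20.71 + 24.04 + 24.04)/3 = 22.93. The sum of squared deviations is 2.22² + 1.11² + 1.11² = 7.39. With SD 11.91 and n = 244, the noncentrality is 244 × 7.39/11.91² = 12.7, which gives power 0.900. The stated 244 reproduces.
- Inflation: 244/0.85 = 287.1, rounded up to 288 per group. This reproduces.
- Discussion: 315 × 0.85 = 267.75, so 268 is the completer count at 15% dropout.

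**2. Patients who leave the comparison at 15% dropout.**
- On 945: 0.15 × 945 = 141.75, about 142, leaving about 803 (268 per arm).
- On 3 × 288 = 864: 0.15 × 864 = 129.6, about 130, leaving about 734 (245 per arm).

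The article's totals do not agree (846, 864 and 945). That is a separate matter and does not change the proportion.

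**3. Observed values discarded.** The timing of dropout is not stated, so only a range can be given. I assume every patient has a baseline value. If all 142 leave before the end-of-treatment assessment, no post-baseline value is lost through the deletion. If all 142 miss only one visit, 142 × 2 = 284 observed post-baseline values are discarded, out of 945 × 3 = 2,835 scheduled, or 10%.

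**4. Power at that loss.** Pooled SD = √((11.91² + 11.83²)/2) = 11.87; difference 24.04 − 20.71 = 3.33.
- 268 per arm: standard error 11.87 × √(2/268) = 1.025; 3.33/1.025 − 1.96 = 1.29; power about 0.90.
- 315 per arm, no loss: standard error 11.87 × √(2/315) = 0.946; 3.33/0.946 − 1.96 = 1.56; power about 0.94.

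So the pairwise target of 90% still holds with completers only. On the 288 basis, the 245 completers meet the 244 needed for the three-group test.

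**5. Bias, for illustration only.** If a share p of an arm drops out and would score g points worse than those who stay, the completers' mean lies p × g below the mean of the whole arm. The value g = 5 is assumed; it is not in the documents. Then p × g = 0.15 × 5 = 0.75 points, or 0.75/3.33 = 23% of the planned difference. A higher NPQ is worse, so the sign depends on the arm:

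| Dropouts 5 points worse than stayers in | Apparent OAT advantage (true 3.33) |
|---|---|
| neither arm | 3.33 |
| control only | 3.33 − 0.75 = 2.58 |
| OAT only | 3.33 + 0.75 = 4.08 |
| both arms alike | 3.33 |

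The same assumed gap can shrink the effect, enlarge it or leave it unchanged.

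**The case against.** **The article names a model, not an analysis set.** Missing-data rules are commonly left to the full protocol or analysis plan, which are not shown. An ANOVA can be run on imputed data with every patient kept, and SPSS also offers a mixed model procedure. This limits the claim to the method as written. It does not remove it, because the named model has a complete-data requirement built in and a further step would be needed to repair it.

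**A reader might infer that the Discussion confirms a completers-only analysis set.** It does not. The 268 is a sample-size target, 85% of 315, and defines no analysis population.

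**A reader might infer a loss of power.** Independent missingness of 8% or 10% at each of three post-baseline visits would keep 0.92³ = 78% or 0.90³ = 73% of patients, with pairwise power of about 87% or 85%. Those losses of 22% and 27% exceed the plan's own 15% maximum, and the independence is assumed. A rate of 5% per visit keeps 0.95³ = 86%, or 270 of 315, which is within the budget. The power argument falls.

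**A reader might infer a bias in favour of OAT.** The documents do not support a direction. Loss of poorly responding controls would make the remaining controls look better and so work against OAT. Several features also reduce the risk: patients are blinded and the blinding is checked, follow-up attendance is subsidised for travel and lost income, and the shallow group receives intradermal needles by the same method as OAT, so the two control arms are not alike in how little treatment they get. All of this stands. It makes differential dropout less certain but does not exclude it.

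**Conclusion.** The point holds in a limited form. The efficacy analysis named in the article, run as written and without prior imputation, excludes every patient with an incomplete set of four visits. At the planning maximum that is about 142 of 945 (about 130 of 864 on the smaller total), with up to about 284 observed post-baseline NPQ values discarded, depending on when patients leave.

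The consequence is wasted data and openness to attrition bias, not a shortfall in power. The 15% is a tolerance, not an observed rate. Dropout unrelated to outcome would cause no bias, and the 23% shift shown above rests wholly on an assumed 5-point gap in one arm. The change is still worth making, because a better method is at hand for almost no cost.

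**What to change.** Replace the repeated measures ANOVA as the main NPQ analysis with a likelihood-based linear mixed model of the three post-baseline values. Its terms should be arm, visit, arm-by-visit interaction and baseline NPQ as a covariate, with an unstructured covariance. Analyse patients in the arm to which they were randomised and use every observed visit. The model is valid if data are missing at random given what was observed, a weaker condition than the complete-case ANOVA generally needs. It recovers patients who miss some follow-up visits. It cannot recover an outcome for those with no post-baseline NPQ, whose number should be reported by arm.

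Keep the complete-case ANOVA as a supportive analysis. Optionally add a sensitivity analysis for data not missing at random, such as a delta adjustment varied separately in each arm, since the bias could run either way.

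The cost is a little more analysis work. SPSS has a mixed model procedure, and no new data or visits are required. The Trial status section says that recruitment and follow-up are under way, and the statisticians are blinded, so the change can be fixed before unblinding.

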### Outcomes

Three well-recognized patient-reported outcome (PRO) tools are used to measure the effect outcomes. The Northwick Park Neck Pain Questionnaire (NPQ) is used as the primary outcome measure, and the McGill Pain Questionnaire (MPQ) and the Medical Outcomes Study Short Form 36 (SF-36) are used as secondary outcome measures.

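### The repeated measures ANOVA counts baseline NPQ as one of its four outcome levels, so its treatment main effect estimates only 75% of the mean post-treatment difference, and no primary term or visit is named

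*Protocol article*

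**What the plan says.** The Outcomes section fixes the endpoint: "The Northwick Park Neck Pain Questionnaire (NPQ) is used as the primary outcome measure".

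The section on the outcome measuring procedure gives the schedule. Outcomes are taken "before the first treatment (baseline measurement), immediately after the final treatment (short-term outcome of therapeutic effect") and then "at the end of the first and third months after the final treatment (long-term effective outcomes"). That makes four occasions, one of them before treatment and three after it. None is ranked above the others.

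The Statistical analyses section says "There are four measuring points set to assess the efficacy of the OAT, as described above in the Outcomes section", and draws from this a two-factor "repeated measures analysis of variance (ANOVA) model with the time of measure as the within-subjects factor", with treatment between subjects and a two-sided level of 0.05. It mentions no baseline covariate, and it does not say which term of the model carries the primary conclusion. The abstract describes the analysis as "repeated measures of analysis of variance (ANOVA) for primary and secondary outcomes of group and time differences", which names group and time but not their interaction.

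The sample size section uses a single NPQ mean per arm: 20.71 (SD 11.91) for OAT and 24.04 (SD 11.83) for both controls. It arrives at 244 per group for 90% power.

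**The concern.** A baseline score cannot carry a treatment effect. When it enters the model as a level of the time factor, the between-subjects treatment term averages one occasion with no expected difference together with three that may have one. The group difference reported from that term is then smaller than the effect patients experience after treatment, and it is not the quantity used to size the trial.

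The baseline score is also strongly informative about later scores if visits are well correlated. The main effect puts that information into the outcome average instead of using it to remove between-patient variation.

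The same model contains a second candidate test, group by time, which behaves quite differently. Because the article does not say which term is primary, a reader cannot tell whether the headline result will be the diluted average or an omnibus test without a direction. The article's hypothesis (Interventions section) is that OAT is superior to both placebo and non-specific effects, and the Discussion asks whether it is superior to the control treatments. Those questions need a named contrast.

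**Working it through.** **Inputs from the article.** Means 20.71 and 24.04, so d = 24.04 − 20.71 = 3.33. Pooled SD = √[(11.91² + 11.83²)/2] = 11.87. n = 244 per group, two-sided α = 0.05, planned power 0.90.

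**Assumptions.** The article gives no correlation between NPQ measurements. I assume an equal correlation ρ between all pairs of visits, shown for 0.3, 0.5 and 0.7, a constant SD, and a difference of 3.33 at each post-treatment visit.

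**Step 1: the plan's own figure.** For a three-group one-way F test at a single time point with means 20.71, 24.04 and 24.04, the noncentrality is λ = n · (2/3) · d²/SD² = 244 × 0.667 × 3.33²/11.87² = 12.80. Power is 0.902. The smallest n reaching 90% is 242 to 244 for SDs of 11.86 to 11.91. The stated 244 is therefore reproduced as a comparison at one time point.

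**Step 2: the dilution.** If the post-treatment differences are e1, e2 and e3, the four-level main effect has expectation (0 + e1 + e2 + e3)/4 = 0.75 × (e1 + e2 + e3)/3. This holds for any time course. With 3.33 at every post-treatment visit it gives 0.75 × 3.33 = 2.50.

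**Step 3: variances, as multiples of SD².**
- Mean of four visits: (1 + 3ρ)/4
- Mean of three post-treatment visits: (1 + 2ρ)/3
- The same mean adjusted for baseline: (1 + 2ρ)/3 − ρ²
- One visit adjusted for baseline: 1 − ρ²

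**Step 4: power of the three-group F test at 244 per group.** Here λ = n · (2/3) · (effect)²/(SD² × variance multiple). For group by time with 6 df, λ = n · (2/3) · 0.75 · d²/[SD²(1 − ρ)].

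| Analysis | ρ = 0.3 | ρ = 0.5 | ρ = 0.7 |
|---|---|---|---|
| Four-level main effect (2.50) | 94.5% | 86.8% | 78.3% |
| Post-treatment mean, unadjusted | 99.5% | 98.1% | 95.6% |
| Post-treatment mean, baseline-adjusted | >99% | >99% | >99% |
| One visit, baseline-adjusted | 92.8% | 96.7% | 99.7% |
| Group by time, 6 df | 80.2% | 92.9% | 99.6% |

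Simulation of the four-level main effect (4,000 runs per ρ) gave 94.9%, 87.9% and 77.8%.

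**Step 5: where the main effect falls short.** It matches the single-visit test of Step 1 when 0.75² = (1 + 3ρ)/4, that is ρ = (4 × 0.5625 − 1)/3 = 0.417. Above a ρ of about 0.42 its power is below the stated 90%.

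**Step 6: cost in patients.** The ratio of required sample sizes, four-level main effect to baseline-adjusted post-treatment mean, is [(1 + 3ρ)/4]/0.5625 divided by [(1 + 2ρ)/3 − ρ²]. It is 1.90, 2.67 and 4.44 at ρ = 0.3, 0.5 and 0.7.

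**The case against.** The strongest reply is that the article never makes the treatment main effect its primary test. In a two-factor model of this kind group by time is the usual treatment test. It uses baseline as the reference and is not diluted. This stands in part: it would be wrong to infer that the whole model wastes the baseline, or that a diluted result is certain. But the article does not name the interaction, and the abstract speaks only of group and time differences. The interaction also has 6 df over three arms and four visits, so a significant result gives no direction, visit or comparator.

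A second reply is that the power loss depends on an unknown ρ. This stands. At ρ = 0.3 the four-level main effect (94.5%) does better than ANCOVA at a single visit (92.8%). With the 268 completers per arm named in the Discussion, its power at ρ = 0.5 is 89.9%, close to 90%. It does not do better than the baseline-adjusted post-treatment mean at any ρ examined.

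Two stronger readings are tempting. A reader might infer that OAT could be declared effective on any of three visits against either of two controls, with inflated family-wise error. The article plans no such set of tests, so no error rate can be attached to it. A reader might also infer that end of treatment must be the primary visit. The article labels that visit short-term and the later ones long-term, without ranking them.

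A full analysis plan, not shown here, could name the visit or the term. The four-level outcome, however, is stated in the article itself.

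**Conclusion.** The point holds in a limited form. Under randomization the treatment main effect of the planned model has an expectation of 75% of the mean post-treatment difference, 2.50 instead of 3.33 points. That ratio needs no assumption about correlation or time course. It is measured against the post-treatment average; against any single visit it would depend on the time course.

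The dilution is conservative: the expected main effect is still zero when there is no treatment effect, so it creates no false claim for OAT. Nor does it equal a 25% loss of power, because averaging four visits also lowers the variance. The power consequence rests on the assumed ρ, equal correlation and constant SD, and it drops below the planned 90% only above a ρ of about 0.42. The advantage of the baseline-adjusted post-treatment mean holds over the whole range examined. The missing choice of primary term adds to the problem, since the two candidate terms differ in power and in meaning. Severity: should fix.

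**What to change.** Before unblinding, take baseline NPQ out of the outcome vector and use it as a covariate. One suitable form is a linear mixed model of the three post-treatment visits with arm, visit, arm by visit and baseline by visit. State one primary estimate: either the baseline-adjusted mean over the three post-treatment visits or one visit chosen by the sponsor. Report it for OAT versus sham and for OAT versus shallow acupuncture, since the hypothesis concerns both controls. If a single visit is chosen, an ANCOVA at that visit and the mixed model need not give the same answer when visits are missing, and a 15% dropout is allowed for, so name which one is primary. The remaining visits can be reported as secondary.

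The cost is analysis wording only. All four measurements are already scheduled, and the Blinding section keeps the statisticians blinded until the final analysis report is complete, so the change can still be prespecified.
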